# **SUMMARY**

Inhaled nitric oxide in neonates with elevated A-a DO2 gradients not requiring mechanical ventilation

**Objective:** This is a pilot study to evaluate whether administration of nitric oxide gas by oxygen hood at 20 ppm significantly increases PaO2, as compared to placebo gas (oxygen), within one hour of initiation, and with no significant adverse effects.

**Study design:** Single center, masked, placebo-controlled randomized crossover trial

**Sample Size:** Total 40 (two groups of 20 each)

**Eligibility criteria:**

*Inclusion criteria:*

1. Gestational Age >34 weeks

2. Age < 48 hrs

3. A-a DO2 >500, <600 on two arterial blood gases one hour apart, while on 100% O2 by oxygen hood

4. Arterial access (post-ductal)

5. Admitted to UAB Regional NICU (Inborn or Outborn)

*Exclusion criteria:*

1. Cardiac disease other than PDA or PFO
2. Rapid deterioration requiring mechanical ventilation before entry into the study
3. Major malformations
4. Major neurologic or metabolic disorder or other illness leading to hypoventilation and hypercarbia

**Study intervention:** After obtaining informed consent, neonates will be randomized to either placebo (oxygen) or NO 20 ppm. The treatment gas will be administered in the inner hood of a double hood system. FiO2 and NO/NO2 concentrations will be monitored continuously. Scavenging will be done by a suctioning apparatus in the outer hood. Respiratory therapists will adjust flow and blending to administer 20 ppm of NO or an equivalent flow of O2. Physicians and nurses caring for the patient and analyzing results will be blinded to patient assignment. After completion of one hour on the study, the gas will be weaned over the next four hours, then discontinued. If at the end of the study period the infant still meets entry criteria, he/she will be crossed over into the other treatment group. The attending physician can initiate mechanical ventilation at any point during this study, based on clinical or other grounds.

**Study measurements:** Arterial blood gases (ABGs; post-ductal) will be obtained just before initiation (0 hrs) and every hour for the next six hours. ***The PaO2 after exposure to one hour of the treatment gas will be the primary outcome measure***. Continuous pulse oximetry will also be performed. Assessment will be made for any “rebound phenomenon” in oxygenation and any adverse effects, including methemoglobinemia, bleeding tendencies, and thrombocytopenia (platelet count before and after the study).

**Sample size estimate:** Repeated measures ANOVA or unpaired t-test will be used if data are normally distributed, otherwise non-parametric tests will be used. The power of the study is 85% with n=20 in each group, =0.05, assuming we need to detect a difference inPaO2 of 25% with a standard deviation at 0.25 of mean. Small numbers are required since this is a pilot study to demonstrate physiologic efficacy and safety, and is not a study to demonstrate effect on clinical outcomes.

### A: Consent form

B: Data collection form

1. **Introduction and hypotheses**

Severe neonatal pulmonary hypertension continues to affect approximately one in 1000 term neonates, with a mortality rate of >50% in the absence of extracorporeal membrane oxygenation (ECMO), and 10-20% even with the availability of ECMO. Morbidity consisting of severe handicap, intracranial hemorrhage, or deafness, continues to occur in more than 20% in survivors. The most common cause is a maladaptation of the neonatal pulmonary circulation to the extra-uterine environment, which may be either idiopathic or induced by sepsis, meconium aspiration, or asphyxia. Nitric oxide (NO), a vasodilator, can be administered by inhalation to produce effects largely limited to the pulmonary circulation. NO inhalation has undergone multiple phase I and II trials, as well many large multicenter clinical trials in neonates with encouraging results. Analysis of results from three major trials (1-3) indicate that the use of ECMO decreased from 54% to 38%, with no prolongation of total ventilator treatment, hospital stay, or incidence of chronic lung disease (4). However, all controlled studies to date have studied nitric oxide administration to neonates who are already on mechanical ventilation.

Conventionally, neonates with hypoxemia and adequate respiratory effort are first adminstered oxygen by oxygen hood. If oxygenation is inadequate despite a high concentration of inspired oxygen (FiO2) or if respiratory acidosis occurs, the infant is placed on a mechanical ventilator. If oxygenation continues to be inadequate despite increasing ventilator settings, rescue therapies such as inhaled nitric oxide or high frequency ventilation are attempted. Lack of response to these therapies usually results in initiation of ECMO. One of the problems with this plan of management is that mechanical ventilation by itself can lead to or potentiate lung injury and predispose to chronic lung disease. The high mean airway pressures that are often required may also decrease pulmonary blood flow and cardiac output. It is possible that administration of inhaled NO to neonates with abnormal gas exchange earlier, rather than later as a rescue therapy in a moribund state, might accelerate the transition of the circulation from the fetal to neonatal physiology and improve oxygenation. This may in turn decrease the need for mechanical ventilation, its associated morbidity, and perhaps even ECMO.

This study is designed as a pilot study to evaluate the physiologic efficacy (rather than effect on clinical outcomes) of NO administered by hood in improving oxygenation of neonates with elevated alveolar - arterial oxygen gradients (A-a DO2). If this is shown to be achievable, subsequent larger trials can determine if this method of NO administration can decrease the need for mechanical ventilation, ECMO, or other major outcomes.

1.1 Primary outcome measure:

Partial pressure of oxygen in post-ductal arterial blood (PaO2)

1.2 Secondary outcome measures:

1. Alveolar-arterial oxygen gradient (A-a DO2) after one hour of exposure to treatment gas
2. Alveolar-arterial oxygen ratio (A/a O2)
3. Oxygen saturation by pulse oximetry (SpO2)
4. Need for mechanical ventilation
5. Duration of oxygen therapy
6. Methemoglobin level in post-ductal arterial blood (MetHb)*
7. Platelet count*
8. Systemic blood pressure*
9. Environmental NO and NO2 exposure*

(* Safety indicators)

1.3 Hypotheses

The primary hypothesis is that administration of nitric oxide gas by oxygen hood at 20 ppm to neonates with elevated A-a DO2 (500-600 mmHg) significantly increases PaO2, as compared to placebo gas (oxygen), within one hour of initiation, and with no significant adverse effects.

Secondary hypotheses

1. Administration of nitric oxide decreases A-a DO2as compared to placebo gas (oxygen)
2. Administration of nitric oxide decreases A/a O2 as compared to placebo gas (oxygen)
3. Administration of nitric oxide increases SpO2 as compared to placebo gas (oxygen)
4. Administration of nitric oxide decreases the need for mechanical ventilation as compared to placebo gas (oxygen)
5. Administration of nitric oxide at 20 ppm by oxygen hood does not increase duration of oxygen therapy significantly as compared to placebo gas (oxygen)
6. Administration of nitric oxide at 20 ppm by oxygen hood does not increase MetHb significantly as compared to placebo gas (oxygen)
7. Administration of nitric oxide at 20 ppm by oxygen hood does not decrease platelet counts significantly as compared to placebo gas (oxygen)
8. Administration of nitric oxide at 20 ppm by oxygen hood does not decrease mean systemic blood pressure significantly as compared to placebo gas (oxygen)
9. Administration of nitric oxide at 20 ppm by oxygen hood does not increase environmental NO and NO2 significantly as compared to placebo gas (oxygen)

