3.2 Entry and exclusion criteria

*Entry criteria:*

1. Gestational Age >34 completed weeks (>35)

2. Age < 48 hrs

3. A-a DO2 >500, <600, on two post-ductal arterial blood gases one hour apart, while on 100% O2 by oxygen hood

1. Post-ductal arterial access (UAC or posterior tibial or dorsalis pedis arterial line)
2. Admitted to UAB Regional NICU (Inborn or Outborn)

*Exclusion criteria:*

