After entry criteria are met, informed consent is obtained from the parents by either the study coordinator, research nurse, or attending physician/fellow and the neonate will be randomized to either the NO group or control group. The treatment gas will be administered by hood, with the clinicians and nurses blinded to assignment. The apparatus setup at the bedside would be identical for both groups and the NO flowmeter and NO/NO2 concentrations will be masked. FiO2 and NO/NO2 concentrations of the inflow gas will be monitored at the beginning of the study period and the sensors will then be moved to the inner hood. Respiratory therapists will adjust flow and blending to administer 20 ppm of NO or an equivalent flow of O2. FiO2 and NO/NO2 concentrations in the inner hood will be monitored continuously for the study period. Physicians and nurses caring for the patient and analyzing results will be blinded to patient assignment. After completion of one hour on the study, the gas will be weaned every hour over the next four hours (20 ppm at 1 hour to 10 ppm at 2 hours to 5 ppm at 3 hours to 2.5 ppm to 4 hours to 0 ppm at 5 hours), then discontinued. If marked deterioration (decrease in oxygen saturation of > 5%) is seen during the weaning phase, the treatment gas can be increased to the previous level and can then be weaned subsequently by the same decrement but over two hours. The attending physician can initiate mechanical ventilation at any point during this study, based on clinical or other grounds. If methemoglobinemia (MetHb>5%) occurs, or if NO2 concentrations are >3% in the inner hood, or if oxygenation decreases significantly (decrease in oxygen saturation of > 5%), or if other adverse reactions that could possibly be related temporally to the treatment gas are evident, the gas is to be weaned in a shorter timespan (50% every 15 minutes). The results of these neonates will still be analyzed based on "intention to treat". If at the end of the study period the infant still meets entry criteria, he/she will be crossed over into the other treatment group.

Monitoring:

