3.7 Study exit criteria

1. Completion of one hour on treatment gas followed by weaning to 100% oxygen by hood. If at the end of the study period the infant still meets entry criteria (A-a DO2 500- 600 mm Hg), he/she will be crossed over into the other treatment group.
2. If methemoglobinemia (MetHb>5%) occurs, or if NO2 concentrations are >3% in the inner hood, or if oxygenation decreases significantly (decrease in oxygen saturation of > 5%), or if other significant adverse reactions that could possibly be related temporally to the treatment gas are evident, the gas is to be weaned in a shorter timespan (50% every 15 minutes).
3. Sudden marked deterioration in any physiological variable, that in the opinion of the attending physician, requires initiation of mechanical ventilation or ECMO (initiation of inotropic support, change of intravenous fluid intake, or antibiotic therapy are not included in exit criteria).
4. Transfer to another institution / death / withdrawal from study by parent or attending physician

The study coordinator is to be contacted in cases where criteria 2, 3, or 4 are being considered.

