3.9 Statistical issues

The power of the study is 85% with n=20 in each group, =0.05, assuming we need to detect a difference of 25 % with a standard deviation at 25% of the mean. Repeated measures ANOVA or unpaired t-test will be used if data are normally distributed, otherwise non-parametric tests will be used. Data will be analyzed by intention to treat. Small numbers are required since this is a pilot study to show physiologic efficacy of the technique and is not meant to study clinical outcomes.

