**4. Ethical considerations**

1. Is NO safe to administer by oxyhood? : 20 ppm of NO has been safely administered during mechanical ventilation to many neonates and infants over the last few years. Administration by oxygen hood, when the concentration of inhaled NO is being continuously monitored, is probably as safe or even safer than administration during mechanical ventilation, since the additional hazards of barotrauma/volutrauma of mechanical ventilation are not superimposed.
2. Is it ethical to withdraw NO after a one hour administration at 20 ppm? : Since this is a pilot study to evaluate the physiologic efficacy of the method, and is not an evaluation of long-term NO by oxyhood on clincal outcomes, it is ethical to wean off NO to 100% oxygen by hood, which is the established practice.
3. Is it ethical to use oxygen rather than nitrogen as the control gas, since the FiO2 of the oxygen group will be higher? : Oxygen is the established and conventional method, and is known to reduce pulmonary arterial pressures. Hence it is ethical to use oxygen rather than nitrogen as the control gas.
4. If weaning from treatment gas is difficult, should treatment be continued on a long term basis? : Again, since this study is to evaluate the physiologic efficacy and not clinical outcomes, and this method of administration is still experimental, we do not favor administration of the treatment gas on a long term basis, although slower weaning can be performed.
5. If a response is seen to the treatment gas, but is not marked, should the treatment gas concentration be increased?: No, most studies have shown that neonates who respond usually do so with 20 ppm. Also, with increasing treatment gas, FiO2 decreases. When the concentration is maintained at 20 ppm or less, FiO2 is more than 95%.
6. Is it ethical to use a control group, since NO is already known to reduce pulmonary pressures and improve oxygenation in mechanically ventilated animals and neonates? : Oxygen is the established and conventional method, and the administration of NO by hood is still experimental. Also, there is provision for a crossover to the other group if the neonate still meets entry criteria after weaning from the treatment gas, so in case of no improvement, the neonate will still access both forms of therapy.
7. **Feasibility**
   1. Available population / estimated recruitment time

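### Secondary hypothesis 5 claims NO does not prolong oxygen therapy compared with oxygen, but the crossover rule gives NO to still-qualifying oxygen-assigned infants while that outcome is running

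*Protocol*

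**What the plan says.** Protocol 1.2 lists "Duration of oxygen therapy" as the fifth secondary outcome, with no period or cut-off. Protocol 1.3 attaches a no-increase claim to it: NO at 20 ppm by hood "does not increase duration of oxygen therapy significantly as compared to placebo gas (oxygen"). No margin is given.

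Protocol 3.4 gives the treatment gas for one hour at 20 ppm, then steps it down hourly to "0 ppm at 5 hours), then discontinued". Protocol 3.7, item 1, describes the normal end of the first gas as "Completion of one hour on treatment gas followed by weaning to 100% oxygen by hood". The crossover rule in 3.4 reads: "If at the end of the study period the infant still meets entry criteria, he/she will be crossed over into the other treatment group". Section 3.7 repeats it with the A-a DO2 range of 500-600 mm Hg. Under 3.2 that range is judged on "two post-ductal arterial blood gases one hour apart, while on 100% O2 by oxygen hood".

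Protocol 4, item 6, gives the reason for the crossover: "so in case of no improvement, the neonate will still access both forms of therapy". Section 3.9 sets the analysis rule: "Data will be analyzed by intention to treat". Sections 3.6 (contamination) and 5.2 (pitfalls) do not mention crossover.

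**The concern.** Hypothesis 5 is a no-harm statement about NO against oxygen, on an outcome that continues past the point where some oxygen-assigned infants are given NO. For them the recorded duration follows exposure to both gases. The comparison by assigned group then answers a different question from the one the hypothesis asks.

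The likely direction of the error is what makes this matter. For a superiority claim, dilution makes success harder. Here the predicted result is no increase, so dilution makes the predicted result easier to obtain. A non-significant difference could be reported as showing that NO by hood does not prolong oxygen therapy, although the oxygen-assigned infants who had not improved had also received NO.

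**Working it through.** **Which comparison the design delivers**

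1. An infant who completes the first gas is on 100% oxygen by hood at 5 hours (3.4 and 3.7, item 1). No completer has stopped oxygen by then, so duration confined to the first gas is about 5 hours in both groups and carries no information.
2. Crossing requires A-a DO2 still at 500-600 on 100% oxygen (3.2, 3.7). Every infant who crosses is therefore still accruing the outcome.
3. Crossing from NO to oxygen does not undo the NO already received. Crossing from oxygen to NO adds NO. Only the second kind alters the contrast.
4. Intention to treat (3.9) therefore compares NO first with oxygen first, then NO if still qualifying.

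**The plan's own power figure**

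Section 3.9 states 85% power for 20 per group, a 25% difference and an SD of 25% of the mean, which is a standardised difference of 1.0. A two-sample t test at two-sided 0.05 (noncentral t, 38 df) gives 86.9%, which agrees to within 2 points. The summary ties this calculation to PaO2. No calculation is given for oxygen duration.

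**Size of the dilution**

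Assumptions, none of them in the protocol:
- c = fraction of the 20 oxygen-assigned infants who cross; 25%, 50% or 75% is 5, 10 or 15 infants
- k = effect of NO given second, relative to NO given first (1 or 0.5)
- D = true lengthening with NO first, set to the value that 20 vs 20 detects with 80% power: 0.909 SD
- (log) duration roughly normal; crossing unrelated to duration in the first table

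The NO group's mean shifts by D and the oxygen group's by c × k × D, so the observed difference is D × (1 − ck). Example with c = 0.50 and k = 1: 0.909 × (1 − 0.50) = 0.455 SD.

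| c | k | Share kept, 1 − ck | Difference (SD) | Chance of a non-significant result |
|---|---|---|---|---|
| 0 | any | 100% | 0.909 | 20% |
| 25% | 1 | 75% | 0.682 | 44% |
| 50% | 1 | 50% | 0.455 | 71% |
| 75% | 1 | 25% | 0.227 | 89% |
| 25% | 0.5 | 87.5% | 0.795 | 31% |
| 50% | 0.5 | 75% | 0.682 | 44% |
| 75% | 0.5 | 62.5% | 0.568 | 58% |

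The second case takes those who cross to be the oxygen-assigned infants with the longest durations (simulation, 40,000 runs). The chance of no significant lengthening at 25%, 50% and 75% crossing is then about 58%, 84% and 94% at k = 1, and about 37%, 52% and 64% at k = 0.5.

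**Without any crossover**

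At c = 0 with 20 vs 20, a true lengthening of 0.5 SD is non-significant 66% of the time, and one of 0.3 SD 85% of the time. Crossover adds to a weakness that the sample size already creates.

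**The case against.** The strongest reply is that hypothesis 5 can be read as a comparison of the assigned groups, which intention to treat delivers validly. Crossover is also conditional. Infants who fall below 500, rise above 600 or go on to ventilation do not cross, and 5.2 expects a significant share to improve quickly. The crossing fraction is unknown and could be small. This stands as a limit on size. It does not rescue the wording, because the hypothesis names NO against placebo oxygen, and the oxygen group as assigned includes later NO by rule.

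A reader might infer that the hypothesis cannot be tested at all and that no analysis could recover the contrast. The documents do not support that. Treatment-switching methods exist (inverse-probability-of-censoring weighting, rank-preserving structural failure time models), although they need strong assumptions and would be imprecise with 40 infants. The analysis plan is not shown. Simple censoring at crossover is no remedy, because it removes infants precisely for still needing 100% oxygen.

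A reader might also infer that mixing must pull the difference toward zero. It does so only if NO given second acts in the same direction in the infants who cross. If NO affects only infants who would not cross, the full difference is kept; if only those who would cross, almost none is.

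Two further points are fair. A lengthening of 0.91 SD is a reference value for the calculation, and nothing in the protocol suggests an effect of that size. The protocol also says it is a pilot not meant to study clinical outcomes, and oxygen duration is not one of its starred safety indicators. Both lower the impact. The directional claim is nevertheless in the protocol and invites a reported conclusion.

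**Conclusion.** The point holds in a limited form. Hypothesis 5 states NO against oxygen; the design compares NO first with oxygen first and conditional NO about 5 hours later. The amount of dilution depends on the unstated crossing fraction and on how NO given second acts. Over the values tried with crossing unrelated to duration, the non-significance rate for a 0.91 SD lengthening goes from 20% to between 31% and 89%. With no crossing there is no loss.

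Even without crossover, a non-significant difference at 20 vs 20 would be weak evidence of no harm, so crossover is not the only reason to avoid that reading.

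The finding does not extend to the primary outcome, since first-gas PaO2 at 1 hour is read before any crossover. Nor is it about the starred safety indicators. A reader might infer that need for mechanical ventilation should be confined to the first gas. That is a separate hypothesis, affected only if events are counted after crossover, and nothing here requires changing it. The change is worth making because it is cheap and prevents an unsupported no-harm statement.

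**What to change.** Reword hypothesis 5 in 1.3 along these lines: Duration of oxygen therapy will be described for infants starting with NO and for infants starting with oxygen, who receive NO about 5 hours later if they still meet entry criteria.

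Add to 3.9: Duration of oxygen therapy will be reported by assigned first gas with a 95% confidence interval and the number of infants crossed in each group. Because crossed infants receive both gases before oxygen stops, a non-significant difference will not be read as showing that NO does not prolong oxygen therapy.

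This costs one reworded hypothesis and two sentences, with no extra infants or samples. The crossover stays as it is, so the access promised in section 4 is kept. The downside is that the trial gives up a no-harm claim on oxygen duration.

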3.4 Apparatus, protocols, and monitoring

Apparatus:

We have developed a "double-hood" model for the administration of NO via oxygen hood. The oxygen/NO/N2 blend is administered to inner hood and
suctioned out of outer hood (and inner hood via NO/NO2 sensors). The inner hood is made of Plexiglas (Olympic oxyhood; 10 inch diameter) and the outer hood is made of plastic sheeting (NOVA tenthouse oxygen tent; 12 x 12 x 10 inch).

100% oxygen (15 lpm) is blended with a NO/nitrogen mixture (800 ppm NO; balance N2) to yield a final concentration of 24 ppm NO, NO2 0.25 ppm, 97 % oxygen, 3 % nitrogen. This becomes the flow into the inner hood, from which the neonate breathes.

A suction apparatus is attached to the outer hood which suctions the gases in the outer hood at approximately 4 lpm. The NO/NO2 sensor lead in the inner hood also suctions approximately 4 lpm. Both suction systems are attached to a vented connector attached to the wall suction which entrains room air and is regulated to a negative pressure of –9 to –10 cm H20.

The concentration of NO in the inner hood with this apparatus is approximately 20 ppm, with NO2 0.95 ppm, and 97 % oxygen. The concentrations in the outer hood are: NO 15-17 ppm, with NO2 0.60-1.05 ppm, and 65-77 % oxygen.

On the outer surface of the hood, near the opening, the concentrations of NO are 0.45-0.55 ppm, with NO2 0.00 ppm, and 22-35 % oxygen. Further away from the hood, the oxygen concentration is 21% (same as room air) and NO2 is undetectable (0.00 ppm). NO levels are < 0.25 ppm at more than 12 inches (30 cm) from the hood.

Protocols:

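### The safety clause and secondary hypotheses 5-8 are worded as absence of a significant difference, with no margin, in a sample sized only for a 1-SD effect on PaO2

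*Protocol*

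**What the plan says.** **Hypotheses (Protocol 1.3).** The primary hypothesis joins the PaO2 claim to a clause that there are no significant adverse effects. Secondary hypotheses 5-9 cover duration of oxygen therapy, methemoglobin, platelets, mean blood pressure and environmental NO/NO2. All share one form: NO "does not increase MetHb significantly as compared to placebo gas (oxygen") for methemoglobin, "does not decrease platelet counts significantly as compared to placebo gas (oxygen") for platelets, and "does not increase environmental NO and NO2 significantly as compared to placebo gas (oxygen") for the environment. Section 1.2 stars the last four as safety indicators. Oxygen duration is not starred but is worded alike.

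**Analysis (3.9, repeated in the Summary).** "Repeated measures ANOVA or unpaired t-test will be used if data are normally distributed, otherwise non-parametric tests will be used". No margin, acceptable limit or confidence-interval criterion is attached to any safety measure.

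**Sample size (3.9).** "The power of the study is 85% with n=20 in each group", for a 25% difference with an SD of 25% of the mean. This is the only power statement.

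**Purpose.** The sample size paragraph of the Summary defends the small numbers because "this is a pilot study to demonstrate physiologic efficacy and safety".

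**Thresholds elsewhere.** Sections 3.4 and 3.7 use methemoglobin above 5%, among other events, as a trigger for faster weaning in the individual infant. No hypothesis uses it.

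**The concern.** A hypothesis of no significant difference, tested with a difference test and without a margin, is supported whenever the test fails to reject. Failure to reject is the likely result in a small study, whether or not there is harm. The smaller and noisier the trial, the more easily such a hypothesis is met, which is the wrong way round for a safety claim.

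At stake is what may be concluded about hood NO in spontaneously breathing neonates. If the report follows the hypotheses, a null safety table would be read as safety demonstrated, when the data may be compatible with an excess of harm that nobody would accept.

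**Working it through.** **Inputs.** n = 20 per arm (Summary, 3.9); allocation 1:1 (3.3); alpha 0.05 (3.9). Sidedness is not stated, so two-sided is used and one-sided is noted. Adverse event rates are not given, so a range is assumed.

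**1. The protocol's own figure.** Standardized difference d = 25%/25% = 1.0. The two-sample t-test has noncentrality d/√(2/n) = 1.0/√(2/20) = 3.162, with 38 df and critical t = 2.024. Power is 86.9%, which agrees with the stated 85%. That figure is for a full 1-SD effect on PaO2 and nothing else.

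**2. Adverse events (the clause in the primary hypothesis).** With no events on control and k on NO, two-sided Fisher p = 2·C(20,k)/C(40,k):
- k = 4: 2 × 4845/91390 = 0.106
- k = 5: 2 × 15504/658008 = 0.047

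So with none on control, five events are needed. If the true control rate is 0, the chance of a non-significant result is P(X ≤ 4) for X ~ Bin(20, p): 63% at p = 20% and 83% at p = 15%. For other control rates, summing over both binomials:

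| True rates (assumed) | Non-significant |
|---|---|
| 0% v 20% | 63% |
| 5% v 25% | 70% |
| 10% v 30% | 76% |
| 20% v 40% | 81% |

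One-sided Fisher gives 62-66% for control rates of 0-10%. The uncorrected chi-square would miss 0% v 20% only 41% of the time, but expected counts there are about 2 per cell, so it is not a suitable test. At 5% v 25% it already misses 56%.

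**3. Continuous measures (hypotheses 5-8).** For a true worsening of 0.5 SD, unpaired, noncentrality is 0.5/√(2/20) = 1.581. Power is 33.8%, so it is missed 66% of the time (54% one-sided). For 80% power the shift must be about 0.91 SD.

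Section 3.4 collects methemoglobin at 0 and 1 h, platelets before and after, and continuous blood pressure, so baseline adjustment is possible for these three. With baseline correlation r, the effective difference is 0.5/√(1 − r²), on 37 df:

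| r (assumed) | Effective d | Missed |
|---|---|---|
| 0.5 | 0.577 | 57% |
| 0.7 | 0.700 | 42% |
| 0.8 | 0.833 | 27% |

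Oxygen duration has no baseline, so 66% stands for hypothesis 5.

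**4. What the sample can say.** With 0 of 20 events, the upper 95% limit is 1 − 0.05^(1/20) = 13.9% one-sided, or 1 − 0.025^(1/20) = 16.8% two-sided. An unadjusted between-group difference has a 95% CI half-width of 2.024 × √(2/20) = 0.64 SD.

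**5. Hypothesis 9.** Section 3.4 places the room measurement 30 cm from the hood. The bench result there is only a bound: "NO levels are < 0.25 ppm at more than 12 inches (30 cm) from the hood". A difference test against the oxygen arm answers whether NO leaks at all. It does not answer whether exposure is acceptable.

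**The case against.** **No sentence says that p > 0.05 establishes safety.** This is correct. A reader might infer a declared decision rule, but the protocol contains none, and section 3.9 assigns no test to safety. The protocol also uses the word significant clinically: sections 3.4 and 3.7 gloss a significant fall in oxygenation as a saturation drop of more than 5%. The adverse-effects clause could be read that way. Hypotheses 5-8, phrased as comparisons with placebo, are harder to read so. If a clinical meaning is intended, no size is given and the hypothesis cannot be tested. What stands is that the wording, with difference tests and no margin, leaves no other criterion.

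**It is a pilot with individual safety triggers and continuous monitoring.** These protect infants during treatment. They are not between-group criteria. Pilot status favours estimation over a claim of demonstration.

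**Interval reporting belongs to an analysis plan.** Largely true, and such a plan may exist. The hypothesis wording and the claim to demonstrate safety are fixed in the protocol.

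**Baseline data and crossover add power.** Baseline adjustment does help, hence the range in step 3. Crossover is limited to infants who still meet entry criteria, so it cannot be relied on.

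**The link to larger trials.** A reader might infer that a null safety result would release the next trial. The introduction ties later trials to improved oxygenation, and no go/no-go step rests on hypotheses 5-9.

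**Hypothesis 9.** A reader might infer that a trivial NO rise is bound to be significant. The clearly non-zero bench values (0.45-0.55 ppm) are at the hood surface, whereas at more than 30 cm only an upper bound is given. That stronger claim is not supported.

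**Conclusion.** The point holds as a defect of hypothesis wording. The safety clause and hypotheses 5-8 can be satisfied by an uninformative null, in a study powered only for a 1-SD PaO2 effect and described in its Summary as demonstrating safety.

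The event figures (63-76%) bear only on the general adverse-effects clause. They rest on assumed control rates of 0-10%, a 20-point absolute excess and Fisher's test at two-sided 0.05. The continuous figures bear on hypotheses 5-8: 66% unpaired, and about 27-57% where a baseline is collected, at assumed correlations of 0.8 to 0.5. The hypothesis 9 point is secondary.

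**What to change.** - In 1.3, remove non-significance as the safety conclusion from the primary hypothesis and hypotheses 5-8. State instead that differences in methemoglobin, platelets, blood pressure and oxygen duration will be estimated with 95% confidence intervals, baseline-adjusted where a baseline is collected.
- Report the number and proportion of infants in each arm with methemoglobin above the protocol's existing 5% threshold, with an exact upper confidence limit. Do not compare a group mean with 5%: the mean can lie well below it while individual infants exceed it.
- In the Summary, replace the claim to demonstrate safety with what 20 treated infants can exclude: if no event of a given kind is seen, a risk above about 14% (one-sided 95%) or 17% (two-sided).
- For hypothesis 9, report NO and NO2 measured at 30 cm against an exposure limit that the sponsor states. The protocol gives no figure for one.

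The cost is wording and a few intervals from data already collected. Sample size, visits and treatment are unchanged, and the safety claim becomes more modest.
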